# Cluster-randomized trial of monthly malaria prophylaxis versus focused screening and treatment: a study protocol to define malaria elimination strategies in Cambodia

**DOI:** 10.1186/s13063-018-2931-x

**Published:** 2018-10-16

**Keywords:** Malaria, Elimination, Cambodia, Dihydroartemisinin-piperaquine, Primaquine, Permethrin, Mass drug administration

## Abstract

**Background:**

Malaria remains a critical public health problem in Southeast Asia despite intensive containment efforts. The continued spread of multi-drug-resistant *Plasmodium falciparum* has led to calls for malaria elimination on the Thai-Cambodian border. However, the optimal approach to elimination in difficult-to-reach border populations, such as the Military, remains unclear.

**Methods/design:**

A two-arm, cluster-randomized controlled, open-label pilot study is being conducted in military personnel and their families at focal endemic areas on the Thai-Cambodian border. The primary objective is to compare the effectiveness of monthly malaria prophylaxis (MMP) with dihydroartemisinin-piperaquine and weekly primaquine for 12 weeks compared with focused screening and treating (FSAT) following current Cambodian national treatment guidelines. Eight separate military encampments, making up approximately 1000 military personnel and their families, undergo randomization to the MMP or FSAT intervention for 3 months, with an additional 3 months’ follow-up. In addition, each treatment cluster of military personnel and civilians is also randomly assigned to receive either permethrin- or sham (water)-treated clothing in single-blind fashion. The primary endpoint is risk reduction for malaria infection in geographically distinct military encampments based on their treatment strategy. Monthly malaria screening in both arms is done via microscopy, PCR, and rapid diagnostic testing to compare both the accuracy and cost-effectiveness of diagnostic modalities to detect asymptomatic infection. Universal glucose-6-phosphate dehydrogenase (G6PD) deficiency screening is done at entry, comparing the results from a commercially available rapid diagnostic test, the fluorescence spot test, and quantitative testing for accuracy and cost-effectiveness. The comparative safety of the interventions chosen is also being evaluated.

**Discussion:**

Despite the apparent urgency, the key operational elements of proposed malaria elimination strategies in Southeast Asian mobile and migrant populations, including the Military, have yet to be rigorously tested in a well-controlled clinical study. Here, we present a protocol for the primary evaluation of two treatment paradigms – monthly malaria prophylaxis and focused screening and treatment – to achieve malaria elimination in a Cambodian military population. We will also assess the feasibility and incremental benefit of outdoor-biting vector intervention – permethrin-treated clothing. In the process, we aim to define the cost-effectiveness of the inputs required for success including a responsive information system, skilled human resource and laboratory infrastructure requirements, and quality management. Despite being a relatively low transmission area, the complexities of multi-drug-resistant malaria and the movement of vulnerable populations require an approach that is not only technically sound, but simple enough to be achievable.

**Trial registration:**

ClinicalTrials.gov, ID: NCT02653898. Registered on 13 January 2016.

**Electronic supplementary material:**

The online version of this article (10.1186/s13063-018-2931-x) contains supplementary material, which is available to authorized users.

## Background

Malaria remains a scourge to humankind with 270 million cases and over 600,000 deaths annually [1]. Despite intensive containment and control efforts, multi-drug-resistant (MDR) *Plasmodium falciparum* continues to be endemic in border areas of Cambodia. Over the last several years, reports have highlighted the declining efficacy of artemisinin combination therapies (ACT) within a few years of their introduction as first-line therapies [2–5]. As *P. falciparum* outpaces the development of efficacious antimalarial drugs, the focus has shifted to elimination of MDR malaria on the Thai-Cambodian border [4]. While the current means available to eliminate malaria are admittedly imperfect, waiting to act may result in a setback to recent gains in malaria control because of the increasingly rapid spread of resistance of *P. falciparum* and fewer treatment options being available [6].

To prevent the spread of multi-drug-resistant malaria, elimination is now being widely advocated in Cambodia, particularly in hard-to-reach mobile and migrant populations including the Military, an under-recognized reservoir of disease [2, 7]. Elimination of MDR malaria at the Thai-Cambodian border is critical given its transient populations who have the highest incidence of malaria in the Greater Mekong Subregion (GMS) [8, 9]. Harnessing the Military’s organizational capacity has recently been proposed as a novel strategy to effectively carry out malaria elimination programs in other more vulnerable mobile groups in close proximity along the borders [10, 11]. Such a strategy could be feasibly scaled as part of a national campaign, leveraging military infrastructure and organizational capacity, and emulated by other regional militaries in the GMS if successful.

However, the question remains: to effectively eliminate malaria in these populations, what are the optimal interventions? A potentially large, but as yet poorly defined, group of asymptomatic parasitemic persons poses a particular challenge to identifying the at-risk population [12–14]. Though more recent data in Cambodia suggests otherwise [15, 16], it has been presumed that submicroscopic asymptomatic parasitemias contribute significantly to ongoing transmission and thus constitute an infectious reservoir that must be addressed in low-endemic settings to achieve elimination [15, 17, 18]. If molecular diagnostic testing is needed to identify persons in this reservoir, or if medical follow-up requirements are too intense to support, large-scale implementation may be difficult or impossible in austere, remote locations. This conclusion has also been suggested by focused screen-and-treat programs as well as reactive case detection strategies in low-transmission areas of Cambodia in civilian populations [19–21].

Unfortunately, the only licensed, available drug able to prevent transmission of the parasite from human to mosquito, primaquine (PQ), can cause severe, life-threatening hemolytic anemia in persons with glucose-6-phosphate dehydrogenase (G6PD) deficiency, and requires effective screening tests that can be easily deployed at the point of care. To permit the greatest possible simplicity and cost-effectiveness during scale-up in resource-poor areas along the border, the ideal approach would require minimal medical monitoring or follow-up visits. Suitability for scale-up will also need to be assessed for operational feasibility, perception of risk among participants, cost and cost-effectiveness of interventions, and alignment with stakeholder values and policy.

### Aim and objectives

We present a pilot operational research protocol to investigate the effectiveness of monthly prophylactic drug administration compared to a focused screen-and-treat approach to inform a regional malaria elimination initiative by the Royal Cambodian Armed Forces (RCAF).*Primary objective*: to compare the effectiveness of focused screening and treatment (FSAT) following current national treatment guidelines versus monthly malaria prophylaxis (MMP) with dihydroartemisinin-piperaquine (DHA-PIP) in combination with weekly primaquine (PQ) (22.5 mg) as transmission-blocking and radical curative agent to reduce the risk of malaria infection in personnel residing in military encampments on the Thai-Cambodian border*Secondary objectives*:◦ To estimate the incremental benefit of wearing a permethrin insecticide-treated uniform (ITU) over drug therapy and existing vector control interventions compared to a sham insecticide-treated uniform (sITU) treated with water. Civilian participants will have comparable selected outer garments treated◦ To define the proportion of asymptomatic carriers of malaria in the population, including the cumulative incidence and incidence density of microscopic and submicroscopic blood-stage parasitemia and gametocytemia◦ Additional secondary objectives can be found in Table 1/Additional file 1

**Table 1 Tab1:** Outcomes

Objectives	Outcomes/endpoints
Primary	
To compare the effectiveness of focused screening and treatment (FSAT) following current national treatment guidelines versus targeted monthly malaria prophylaxis (MMP) with DHA-piperaquine in combination with low-dose weekly primaquine (PQ) (22.5 mg) for 12 weeks	Absolute risk reduction in a cluster based on those individuals’ polymerase chain reaction (PCR)-corrected absence of parasitemia at the end of 6 months in the MMP versus FSAT clusters
Secondary	
Estimate the incremental benefit of insecticide-treated uniforms (ITU) over drug therapy and existing vector control interventions compared to a sham insecticide-treated uniform (sITU)^a^	Absolute risk reduction in a cluster based on those individuals’ PCR-corrected absence of parasitemia at the end of 6 months^a^ Proportional landings of mosquitoes on treated uniform’s swatch side of cages
Assess the effectiveness of presumptive anti-relapse and transmission-blocking therapy with weekly low-dose primaquine (22.5 mg)^a^	Incidence of *P. vivax* recurrent infection and PCR-corrected *P. falciparum* recrudescence^a^ PCR-corrected absence of gametocytemia^a^
Evaluate the safety and tolerability of blood-stage antimalarials and weekly low-dose primaquine at 12 weeks versus 8 weeks in treated MMP and FSAT volunteers, respectively	Number of hemolytic events or other serious adverse events in participants over 13 years of age receiving primaquine
Assess level of antimalarial drug resistance at the selected study sites	Number of all-species malaria recurrence, established molecular markers of drug resistance, and clinical failure rates based on WHO criteria
Define the proportion of asymptomatic carriers of malaria in the study population	Cumulative incidence and incidence density of PCR-corrected parasitemia and submicroscopic parasitemia in each arm
Define the epidemiology of malaria infection in volunteers developing malaria	Cumulative incidence and incidence density of parasitemia
Compare the sensitivity and specificity of the currently recommended malaria rapid diagnostic test of choice in Cambodia with RT-PCR	Retrospective assessment of the proportion of asymptomatic carriers that would have been missed by each test and an estimate of the incremental cost-effectiveness of each test
Compare sensitivity and specificity of two currently available rapid diagnostic tests to detect moderate to severe G6PD deficiency using quantitative G6PD testing as the reference standard	Retrospective assessment of the proportion of persons with moderate to severe deficiency who would have been missed with each screening modality, and an estimate of the cost-effectiveness of each test
Describe population demographics to include the acceptability of FSAT, malaria prophylaxis, and use of vector control measures among participants, including willingness to participate in future malaria elimination campaigns	Descriptive analysis of participants’ responses to survey questions pre and post study regarding FSAT, malaria prophylaxis, and use of vector control measures
Support host nation capabilities by improving the Royal Cambodian Armed Forces’ (RCAF’s) ability to diagnose, prevent, and treat malaria supported by robust data to achieve malaria elimination	A scalable military malaria elimination “unit of action” will be established at the provincial level, staffed by RCAF personnel trained during the course of the study

^a^Pilot study objective and endpoint added to assess operational feasibility given ongoing community concerns regarding these interventions. These endpoints are statistically underpowered and this data will be used to inform larger studies in the future

Lastly, an overarching aim of this operational study is to increase The Cambodian Military’s capability to diagnose, prevent, and treat malaria, and to understand the population’s willingness to participate in malaria elimination campaigns. To do so, a scalable military malaria elimination “unit of action” is being established at the provincial level, staffed by RCAF personnel who are trained during the course of this study. Regardless of the outcome, the study will provide critically important information to inform elimination policy in Cambodia and the GMS.

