### Treatment intervention

Volunteers randomized to MMP arm aged 13 years and older receive a monthly 3-day treatment course of (DHA-PIP; 360/2880 mg) for 3 months. They will also receive a weekly dose of 22.5 mg of PQ for 12 weeks. Children of 12 years of age or less will receive only a monthly 3-day weight-based treatment dose of DP for 3 months without PQ treatment. In the MMP arm, symptomatic patients or microscopy-confirmed parasitemia in the first 3 months are considered a failure of prophylaxis and treatment is given according to the national treatment guidelines. If the volunteer has parasitemia detectable by PCR only and is symptom free at monthly follow-up, the study treatment with monthly DHA-PIP is continued for 3 months as outlined for the MMP arm. To reduce phlebotomy requirements for G6PD testing and potential hemolytic risk in children, PQ is not be administered to those less than 13 years old.

Volunteers randomized to the focused screening and treatment (FSAT) arm are treated according to current national malaria treatment guidelines if they test positive for malaria based on blood smear and/or real-time PCR results during monthly follow-up. In the FSAT arm, all volunteers with parasitemia detectable with PCR receive antimalarial treatment, even if they are symptom- free.

At the time of protocol development, national treatment guidelines for areas of known piperaquine resistance, to include the designated study regions, recommended a 3-day course of artesunate and mefloquine (A + M) and a single 15-mg dose of PQ for acute *P. falciparum*, or DP for blood-stage *P. vivax* infection. Elimination interventions are carried out monthly during the first 3 months after enrollment, and then followed by 3 months of additional malaria assessment by smear and PCR diagnosis with malaria treatment as necessary following current national treatment guidelines (Fig. 1, Table 2, Fig. 2). Those febrile but negative for malaria are referred for evaluation and treatment of alternative diagnoses.

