### Clinical procedures

Following documentation of informed consent/assent and determination of eligibility, a study physician completes an initial medical history and physical examination (Table 2). Volunteers aged 13 years and older have a rapid diagnostic test (RDT) for malaria, thick and thin blood films to estimate both sexual and asexual parasite densities, and malaria PCR diagnosis. Additional laboratory testing includes a complete blood count (CBC); an estimate of G6PD activity using quantitative testing to be compared with fluorescence and commercially available point-of-care testing; G6PD genotyping; real-time PCR to detect gametocytes; and analysis of molecular markers of resistance for those malaria positive at intake. Children aged 12 years and under have only rapid malaria diagnostic testing, malaria smears and PCR to detect submicroscopic parasitemia, with other testing deferred in children to reduce phlebotomy burden. Children less than 13 years of age are not tested for G6PD deficiency as they are not treated with PQ under this protocol. G6PD-deficient volunteers 13 years and older are counseled regarding the diagnosis, and have a repeat CBC on day 3 (± 1 day) following PQ treatment with repeat testing on day 7, if they have a greater than 10% drop in their hemoglobin or hematocrit, or at any time there are clinical signs of hemolysis.

All volunteers are followed monthly thereafter or at any time that they present with symptoms of suspected malaria, with a brief clinical evaluation and malaria diagnostics to include PCR assays for asexual and sexual parasites. Malaria-positive volunteers aged 13 years and older have additional tests for molecular markers of resistance. At these times, a swatch is taken from the volunteer’s uniform or clothing for repellency monitoring.

At the conclusion of the 180-day (− 2 to + 3 days) follow-up period, volunteers have blood drawn for malaria smears, RDTs, asexual blood-stage and gametocyte PCR diagnosis. If infection is noted at discharge, volunteers will continue to be followed until resolution of infection.

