#### Permethrin clothing treatment

Each uniform is treated by study staff according to the site’s randomization prior to distribution with a single application of the 40% permethrin Individual Dynamic Absorption (IDA) kit from the US Army’s supply system or water only for sham-treated uniforms. Permethrin treatment is designed to last for 30 washings, which should be suitable for the 6-month duration of the study. At enrollment, each volunteer has one to two field uniforms treated, and civilian volunteers have one to two sets of outer covering garments that they wear while in forested areas treated. The number of clothing sets treated will depend on the number in the volunteer’s possession, and additional clothing sets may be treated during the course of the study if/when the volunteer acquires new clothing, or when treated clothing is damaged or becomes otherwise unserviceable.

Monitoring of treated uniform repellency will be performed by taking uniform swatches numbered with the subject’s study ID at monthly intervals for 6 months. The numbered swatches will be sewn into the uniforms at the time of treatment. Blinded entomology technicians will randomly select 5% of uniform swatches, and place them in cages of female mosquitoes to observe for repellency. The clothing swatches will be placed on the wall of the mosquito cages and proportional landings on the swatch side of the cage will be assessed.

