### Sample size rationale

Up to 1200 persons are being enrolled and followed in this cluster-randomized study. The study compares estimates of the absolute risk reduction based on the proportion remaining malaria free at the end of 6 months. We assume that MMP administration combined with an insecticide-treated uniform (ITU) on the background of any pre-existing vector control methods that might be employed will need to reduce malaria incidence to zero by study conclusion to achieve elimination. The MMP approach will be using nearly every currently available intervention in Cambodia to eliminate malaria in this population. Current mathematical models show that multi-round mass drug administration (MDA) can reduce malaria prevalence to less than 10% if high coverage is achieved [27]. Focused screening and treatment alone (FSAT) is assumed to be 50% effective based on a recent study at the same site which found that only 50% of patients treated using an intense screening and treatment approach remained malaria free at the end of 4–6 months of follow-up [2]. The study is, therefore, powered to detect a two-fold difference in effectiveness between the two intervention groups. These are thought to be reasonable assumptions a priori for the purposes of sample size calculations though there has never been a head-to-head comparison of these strategies published in the literature. Given that this will be a stratified analysis, no assumptions regarding vector control measures are included in the calculation. Pre-existing vector control measures that the Military may employ, including ITNs, are assumed to be equally distributed among the overall study population. Permethrin-treated uniform comparisons are a secondary endpoint intended only to estimate a potential additive effect.

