### Statistical methods

The primary study endpoint will be the absolute risk reduction (ARR) with 95% confidence intervals (CIs) based on the proportion of volunteers in each arm with absence of PCR-positive parasitemia at the end of 6 months using an intention-to-treat analysis (Table 1). In addition, logistic regression modeling may be employed to provide multivariate analyses based on other possible study confounders such as age, proportion of children, proportion of pregnant women, etc. The primary study population will be intention-to-treat, defined as all volunteers (both military and civilian family members) who are enrolled at either site. The per-protocol analysis population will include all those volunteers who enrolled and completed follow-up up to 180 days. However, volunteers lost to follow-up that do not complete up to 180 days of follow-up will be excluded from the per-protocol analysis, but included in an intention-to-treat analysis.

Secondary study endpoints are pilot endpoints to include incidence rates, molecular and parasitological endpoints, safety, vector control effectiveness (e.g., permethrin-treated versus water-treated uniforms), and comparison of malaria and G6PD diagnostic modalities. The calculation of incidence rates (attack rate over total time at risk) for prophylactic and FSAT groups will be calculated adjusted and unadjusted with 95% CI. All volunteers completing at least one follow-up assessment will be included in the safety analysis. The safety analysis database will include those volunteers in the set of randomized volunteers who receive at least one dose of study drug. All parasitological data will be included in the parasitological analyses. A stratified analysis comparing the vector control arms within each group will also be compared as those remaining malaria-free at 180 days. Given the possibility of the highly variable nature of transmission at the geographical sites, existing pre-enrollment malaria surveillance data by RCAF and day 1 screening data by AFRIMS will guide if a pair-matched analysis is necessary.

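### Table 1 scores permethrin clothing on PCR status at month 6, Statistical methods on remaining malaria-free; because infections are treated along the way, the two definitions can differ several-fold in events, and no incidence analysis by clothing assignment is stated.

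*Protocol article*

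**What the plan says.** **Endpoint in Table 1.** The insecticide-treated-uniform row uses the same outcome as the primary row: an absolute risk reduction based on "PCR)-corrected absence of parasitemia at the end of 6 months". A footnote marks the uniform endpoint as a pilot endpoint that is underpowered and meant to inform larger studies.

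**Endpoint in Statistical methods.** The clothing comparison is given as "A stratified analysis comparing the vector control arms within each group will also be compared as those remaining malaria-free at 180 days".

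**The same split for the study measure.** Sample size rationale says "The study compares estimates of the absolute risk reduction based on the proportion remaining malaria free at the end of 6 months", whereas Statistical methods defines the primary endpoint by "absence of PCR-positive parasitemia at the end of 6 months using an intention-to-treat analysis".

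**Data collected.** Table 2 schedules malaria PCR at enrolment and at days 30, 60, 90, 120, 150 and 180. Clinical procedures adds "All volunteers are followed monthly thereafter or at any time that they present with symptoms of suspected malaria".

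**Treatment during follow-up.** In the FSAT arm, "all volunteers with parasitemia detectable with PCR receive antimalarial treatment", with or without symptoms (Treatment intervention). After the first three months, both arms are assessed by smear and PCR and treated under national guidelines where needed.

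**Incidence analysis.** Statistical methods plans "The calculation of incidence rates (attack rate over total time at risk) for prophylactic and FSAT groups". Table 1 lists cumulative incidence and incidence density in each arm in one row, and in another without naming groups. None is stated by clothing assignment.

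**Clothing.** "Permethrin treatment is designed to last for 30 washings, which should be suitable for the 6-month duration of the study" (Permethrin clothing treatment). Further sets may be treated during the study.

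**The concern.** The objective is the incremental benefit of wearing treated clothing on top of drug therapy. A volunteer who becomes PCR-positive at day 60, is treated, and is PCR-negative at day 180 counts as a success under Table 1 and as a failure under Statistical methods. Both can be applied to the same dataset and can give different estimates of the clothing effect, so the choice could be made after the results are known.

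The literal Table 1 reading also has a particular weakness. Where detected infections are cleared before the next screen, day-180 status mainly reflects infections acquired since the day-150 screen. It says little about the months before. For an endpoint whose purpose is to inform later studies, a clear definition and the best available precision are most of its value.

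**Working it through.** The protocol gives no sample size or expected effect for the clothing comparison. Its figure of 78 per cluster belongs to the drug-strategy comparison and does not bear on this point.

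**Inputs from the protocol article**
- 50% remaining malaria-free after 4–6 months under screening and treatment; ICC 0.4; 8 clusters (Sample size rationale).
- About 1000 people in 8 encampments (Abstract), so 1000/8 = 125 per cluster.

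**Assumptions made here**
- The 50% is taken as cumulative over six months, with constant hazard.
- Every infection is cleared before the next screen.
- Clothing is split 4 versus 4 clusters (500 per group), with the 50% risk applied to all sham clusters. This is favourable, since the protocol assumes MMP reaches zero incidence.
- Clothing hazard ratio 0.5, and the same ICC for both definitions.

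**Step 1: infections counted.** Monthly hazard h = −ln(0.5)/6 = 0.1155.
- Single month-6 reading: 1 − exp(−0.1155) = 0.109, or 55 of 500.
- Any infection over six months: 1 − exp(−6 × 0.1155) = 0.50, or 250 of 500.
- The single reading keeps 55/250, about 22%.

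With 10% ever infected the counts are 9 against 50 of 500; with 5%, 4 against 25. The share kept is about 17–22% throughout.

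**Step 2: power.** With hazard ratio 0.5 the permethrin risks are 1 − exp(−0.0578) = 0.056 (single reading) and 1 − exp(−0.3466) = 0.293 (cumulative). The differences are 0.053 and 0.207. SE = √{[p₀(1−p₀) + p₁(1−p₁)] × DE/500}, where the design effect DE = 1 + 124 × ICC. The test is a two-sided 5% t-test with 6 degrees of freedom.

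| ICC | DE | SE, single reading | SE, cumulative | Power, single reading | Power, cumulative |
|---|---|---|---|---|---|
| 0.01 | 2.24 | 0.026 | 0.045 | 40% | 97% |
| 0.05 | 7.2 | 0.047 | 0.081 | 16% | 57% |
| 0.4 | 50.6 | 0.123 | 0.215 | 6% | 13% |

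**Step 3: interval width.** Take the per-cluster variance of the log rate as k² + 1/(125hT), with T = 1 or 6 months and k the between-cluster coefficient of variation. At h = 0.1155 the second term is 0.0692 or 0.0115.
- No clustering (k = 0): width ratio √(0.0115/0.0692) = 0.41.
- ICC 0.4 at 50% risk gives k = √(0.4 × 0.5/0.5) = 0.63, so k² = 0.40. Width ratio √(0.412/0.469) = 0.94, about 1.14 times the information.

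At the planning ICC, using every screen narrows the interval by only about 6%.

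**The case against.** The strongest reply is that the single reading is not established. Both the clothing sentence in Statistical methods and the Sample size rationale speak of remaining malaria-free, which would use all monthly screens and lose no infections. That is correct, and it limits the point to two unreconciled definitions. It does not remove the point, because Table 1 is the outcomes table and, followed as written, counts infected-and-treated volunteers as malaria-free.

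A reader might infer more, and the documents do not support it:
- That the other five screens are discarded. They feed the planned incidence analyses; what is missing is a statement that these are done by clothing assignment. The article is condensed, and its additional file and any analysis plan are not shown, so such an analysis may exist there. The mismatch between Table 1 and Statistical methods is in the article itself.
- That the clothing effect rests on a handful of late infections. The protocol's 50% figure implies about 55 per 500 at month 6. Very small counts arise only at low incidence, which is plausible in MMP clusters.
- That the reading falls when the permethrin has worn off. The treatment is said to suit the six months, further sets may be treated, and repellency is monitored monthly. Waning is not shown.

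It can also be argued that an end-of-study reading shares the primary endpoint's scale and time point, and that prophylaxis in months 1–3 suppresses infections that clothing might prevent. Both stand. They support keeping day-180 status as a supporting result and allowing for drug arm. They do not support leaving two definitions in place.

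Finally, this is a declared pilot endpoint on which no decision rests. That lowers the stakes, but the correction is also very cheap.

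**Conclusion.** The point holds in this form: the clothing outcome has a point-in-time definition in Table 1 and a cumulative one in Statistical methods, and the incidence rates that would use all follow-up are stated only for the drug groups. The two definitions differ roughly four- to sixfold in infections counted (55 against 250 per 500 at the protocol's 50%; 4 against 25 at 5%), given constant hazard and clearance between screens. Clearance is less certain in MMP clusters during months 1–3, where symptom-free volunteers positive by PCR alone simply continue the monthly regimen.

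The statistical gain from using all screens is conditional. It is large if clustering is weak and small at the protocol's ICC of 0.4, where the eight clusters limit the comparison more than the choice of visits. It would be wrong to conclude that a cumulative endpoint makes this comparison adequately powered. The main gains are a single definition and an estimate that covers the whole period of wear. The same wording split affects the primary endpoint and should be settled alongside this one.

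**What to change.** Use one definition in the Table 1 uniform row and in Statistical methods:
- **Endpoint:** new PCR-detected infection at any follow-up visit from day 30 to day 180, as cumulative incidence or as a rate over time at risk, by clothing assignment.
- **Analysis:** summarise per cluster, then compare permethrin with sham, adjusted for or stratified by drug arm.
- **Exclusions:** do not count infections present on day 1, or *P. falciparum* episodes genotyped as recrudescent, as new.
- **Supporting result:** PCR status at day 180.

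The cost is wording and analysis only: the PCR results and genotyping are already planned, and incidence rates are already to be computed for the drug groups. There are two small downsides. *P. vivax* relapses cannot be separated from new infections and will dilute the clothing effect somewhat. Prophylaxis in months 1–3 limits the extra information from MMP clusters.
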